### Definitions

On MRI liver lesions are defined as malignant on DWI when they are (moderately) hyperintense at b = 50 s/mm^2^ and remains hyperintense at b = 800 s/mm^2^. A lesion is considered benign when it is hyperintense at b = 50 s/mm^2^ and shows a substantial decrease in signal intensity at higher b values (b = 500 and b = 800 s/mm^2^). If none of the criteria is met, a lesion is classified as indeterminate.

On CECT liver lesions are defined as malignant if they are hypodense, not showing typical features of a simple cyst (fluid attenuation measurements, round-oval, well-defined borders, no contrast enhancement), hemangioma (localization next to vessels, peripheral nodular enhancement, centripetal fill-in), or focal fatty infiltration (geographic hypodense area, angular margins, typical location). If a lesion is showing signs of simple cyst, hemangioma or focal fatty infiltration it is defined as benign. If a lesion is too small to characterize it is classified as indeterminate.

TNM status is classified according to the American Joint Committee on Cancer (AJCC, 8th edition) [28]. Lymph nodes are defined as suspicious if they are rounded and ≥ 5 mm or if they are not-rounded with the shortest axis ≥ 10 mm.

### Safety and ethics

There is a low risk and low burden for patients participating in this study. Patients might benefit from study participation due to possible improvement of detection of liver metastases. The contrast agent used for MRI has few known side effects and rarely leads to a severe allergic reaction [29]. Extra CECT scans might be performed in some study patients with the associated radiation and contrast exposure. Patients diagnosed with pancreatic cancer have a 5-year overall survival of 8%. Radiation-induced cancer has a latency period that substantially exceeds 5 years. Therefore, the health risk for this specific oncologic patient group is almost negligible.

MRI can lead to earlier detection of liver metastases, however in some patients these lesions might be too small to biopsy. Consequently, we cannot always provide the patient certainty about the nature of the liver lesions detected with MRI. Furthermore, in follow-up local recurrence or metastases might be detected before a patient has symptoms. This may be seen as a disadvantage by some individuals.

### Statistics

#### Sample size

The sample size for the study was calculated for the primary endpoint (sensitivity and specificity of MRI for the detection of liver metastases).

The sample size is calculated based on a method for power calculations for diagnostic studies described by Jones et al. [30]. Based on literature and our previously performed retrospective study [9, 31–35] we estimate the sensitivity of MRI will be approximately 90%. In literature the specificity for MRI is usually higher than the sensitivity, therefore we based our sample size calculation on the sensitivity only. With an expected sensitivity of 90%, confidence interval of 95% (Z = 1.96) and α = 0.05, 138 patients with metastasis are required for analysis. Based on literature the expected percentage of patients with liver metastases is approximately 40% [3, 36]. With an expected inclusion rate of 80% (assuming 20% cannot be analyzed optimally, e.g. because no representative liver biopsies could be acquired, mortality before first follow-up or withdrawal) we need approximately 433 patients. In case the proportion of patients with metastases is not equal to 40% in our cohort, we will include until we reach 138 patients with liver metastasis or up to a maximum total of 465 patients.

#### Analysis

Analysis will be done using SPSS (IBM Corp., Armonk, New York, USA). Continuous variables will be summarized with standard descriptive statistics including mean, standard deviation, median, and range. Categorical variables will be summarized with frequencies. A *p*-value less than 0.05 is considered statistically significant.

For the analysis of the diagnostic accuracy (sensitivity and specificity) a 2 × 2 cross tabulation will be made comparing MRI and CECT to histopathology and follow up. Performance of CECT and Gd-enhanced MRI with DWI will be compared using McNemar’s test. We will report the changes made in patient management in a descriptive manner. Median and 1-year survival will be reported. Survival endpoints (disease free survival and overall survival) will be analyzed using Kaplan-Meier plots. Survival curves are compared using the log rank test. We will compare the results of both readers to determine the inter-observer variability. A Cohen’s Kappa (k value) of 0.81–1.00 is interpreted as excellent, 0.61–0.80: substantial agreement, 0.41–0.60: moderate agreement, 0.21–0.40: fair agreement, and 0.00–0.20: poor agreement.

We partly anticipated missing data by introducing the composite reference standard of follow up. Unfortunately, missing data still can occur when, for instance, a patient suspected of having metastatic disease, does not have histopathological confirmation and dies before the composite reference standard follow up could take place. If necessary, additional analysis will be performed to determine the robustness of the results and to deal with missing data.

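### Missing reference results may depend on the MRI result, but the plan leaves any correction of the primary 2 × 2 table to 'if necessary'

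*Protocol article*

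**What the plan says.** Under Analysis, the protocol article builds sensitivity and specificity from a 2 × 2 cross-tabulation of MRI and CECT against histopathology and follow-up. Under Reference standard, histology is sought for indeterminate or malignant lesions seen on CECT and/or MRI. Paired imaging at 3, 6 and 12 months is the alternative for suspected lesions without histological proof.

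The Sample size section expects incomplete data: "assuming 20% cannot be analyzed optimally, e.g. because no representative liver biopsies could be acquired, mortality before first follow-up or withdrawal". The total is inflated accordingly: "we need approximately 433 patients".

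The Analysis section recognises that a reference result can still be missing. Its example is a patient suspected of metastatic disease who "does not have histopathological confirmation and dies before the composite reference standard follow up could take place". It then states the handling: "If necessary, additional analysis will be performed to determine the robustness of the results and to deal with missing data".

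**The concern.** Patients without a reference result cannot be placed in the 2 × 2 table. In the plan's own example, the missing result follows suspicion at imaging, and suspicion at imaging is what the index test measures. The first reason in the 20% allowance, failure to obtain a representative liver biopsy, arises only where a scan has shown a lesion to biopsy. So whether a patient is verified may well depend on the MRI result. Sensitivity and specificity from verified patients alone are then biased. Inflating the total replaces lost numbers but leaves the bias as it was.

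The stated rule defers the decision on a correction until the data are in, without saying what would trigger it or which method would be used. The primary outcome is at stake.

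**Working it through.** **1. The plan's own figures.** The Sample size section states "With an expected sensitivity of 90%, confidence interval of 95% (Z = 1.96) and α = 0.05, 138 patients with metastasis are required for analysis". The half-width is not given. With w = 0.05, n = Z²·Se·(1 − Se)/w² = 1.96² × 0.90 × 0.10 / 0.05² = 138.3, which matches 138. Then 138.3/0.40 = 345.7, rounded up to 346, and 346/0.80 = 432.5, rounded up to 433. Both stated figures reproduce. The division by 0.80 treats the 20% as not contributing to the table.

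**2. Inputs for the bias.**
- N = 433, prevalence 0.40, sensitivity 0.90, 20% unverified (Sample size).
- Specificity: no design value is given. Assumed 0.88 (the 3 T meta-analysis cited in the Discussion) to 0.96 (the lower end reported by the earlier prospective study in the Background).
- Share s of the unverified who are MRI-positive: not given, so varied.
- Loss is assumed random within MRI result.

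**3. Formulas.** With metastases: 0.40 × 433 = 173.2, so TP = 155.9 and FN = 17.3. Without: 259.8, so FP = 259.8 × (1 − Sp) and TN = 259.8 × Sp. Unverified: U = 0.20 × 433 = 86.6. The fraction lost among MRI-positives is a = sU/(TP + FP), and among MRI-negatives b = (1 − s)U/(FN + TN). Then

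Se = TP(1 − a)/[TP(1 − a) + FN(1 − b)]; Sp = TN(1 − b)/[TN(1 − b) + FP(1 − a)].

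**4. One case in full: Sp 0.96, s = 1.** FP = 10.4, TN = 249.4, a = 86.6/166.3 = 0.521, b = 0. Remaining: TP 74.7, FN 17.3, FP 5.0, TN 249.4. Se = 74.7/92.0 = 0.812; Sp = 249.4/254.4 = 0.980.

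**5. Results** (complete-case value, with change in points)

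| MRI-positive share of unverified | Se, if true Sp 0.88 | Se, if true Sp 0.96 | Sp, if true 0.88 | Sp, if true 0.96 |
|---|---|---|---|---|
| 100% | 0.829 (−7.1) | 0.812 (−8.8) | 0.932 (+5.2) | 0.980 (+2.0) |
| 90% | 0.845 (−5.5) | 0.832 (−6.8) | 0.924 (+4.4) | 0.978 (+1.8) |
| 75% | 0.866 (−3.4) | 0.857 (−4.3) | 0.911 (+3.1) | 0.973 (+1.3) |
| 50% | 0.894 (−0.6) | 0.888 (−1.2) | 0.887 (+0.7) | 0.965 (+0.5) |
| 43% / 38% (loss unrelated to MRI) | 0.900 (0) | 0.900 (0) | 0.880 (0) | 0.960 (0) |
| 25% | 0.915 (+1.5) | 0.912 (+1.2) | 0.859 (−2.1) | 0.954 (−0.6) |

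The last row shows the reversal when MRI-negatives are over-represented. At a true specificity of 1.00, the 75–100% cases lower sensitivity by 4.9–10.0 points and leave specificity unchanged.

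**6. Sensitivity to the 20%.** If only 10% are unverified (43.3 patients), sensitivity falls by at most 2.6 (Sp 0.88) to 3.1 points (Sp 0.96), even if all of them are MRI-positive.

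**7. Sensitivity to the mechanism.** If loss depends on true disease status alone, neither measure is biased. If all 86.6 lost patients are true positives, Se = (155.9 − 86.6)/(173.2 − 86.6) = 0.80 and specificity is unbiased.

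**The case against.** The strongest objection is that the documents do not say who the unverified patients are. The 20% comes with three example reasons and no split by MRI result, and the missing-data example is a single illustration. Early death and withdrawal also strike MRI-negative patients, who have no lesion to biopsy and so may be left without any reference result. MRI-positives are routed to ultrasound, biopsy or exploration, and those with histology keep a reference result even if they die early. Suspicion can also come from CECT alone. All of this stands. A reader might infer that the unverified are mostly MRI-positive, or that the direction of bias is known. Neither is in the documents.

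A reader might also infer that the bias exceeds the planned precision. That does not hold in general. The 5-point half-width is back-solved and concerns sensitivity only. The sensitivity bias passes it only if about 86% (Sp 0.88) or 79% (Sp 0.96) or more of the unverified are MRI-positive. The specificity bias passes it only at a true specificity near 0.88 with about 98% or more MRI-positive. At 0.90 or above it stays at 4.5 points or less.

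The 20% is also a planning margin for patients not optimally analysable. The section on specific withdrawal uses that word for patients found not to have PDAC, who are properly excluded. If the margin includes them, fewer than 20% are unverified PDAC patients. Nor does the text say outright that the unverified are dropped; that is implied by the inflation and by the form of the table.

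Finally, this is a journal article, and the detailed method may sit in a full protocol or SAP. That is fair for the choice of method. But the article is not silent: it states a rule, and the rule is conditional on an unstated trigger.

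**Conclusion.** The point holds in this limited form. The plan expects up to 20% of patients not to be optimally analysable, its own missing-data example depends on suspicion at imaging, and the correction is left open until the data are seen. If verification differs by MRI result, the primary estimates are biased whatever the sample size.

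The size is conditional: sensitivity about 3–9 points too low and specificity about 1–5 points too high if 75–100% of a 20% loss is MRI-positive, about 1 point at 50%, nil if loss is unrelated to MRI result, and reversed if MRI-negatives are over-represented. This rests on the plan's 90% sensitivity and 40% prevalence, an assumed specificity of 88–96%, and loss at random within MRI result. Since neither the share nor the direction can be known in advance, the handling should be fixed beforehand.

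**What to change.** Delete 'If necessary' and pre-specify an analysis of all PDAC patients with a baseline MRI that corrects for missing reference status. Two suitable methods are:
- the Begg–Greenes correction, or
- multiple imputation of the reference result from the baseline MRI and CECT calls, lesion number and size, stage, CA19-9 and survival, all of which the plan already records.

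Because suspicion on either scan triggers histology, the imputation model should use both calls. Report the corrected estimates beside the complete-case table, and give the number unverified by MRI result. Add best- and worst-case bounds that vary both groups: unverified MRI-positives as all true or all false positives, and unverified MRI-negatives as all false or all true negatives. Bounds on the MRI-positives alone would leave possible false negatives untouched. If a full protocol or SAP already fixes this, the article's sentence should be aligned with it.

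The cost is a change of wording and a few hours of programming, outside SPSS if needed. The downside is reliance on missing-at-random given the recorded variables. The bounds show how much the result depends on it.

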### Trial status

The first patient was included on December 21st 2017. At the time of protocol submission (July 23th 2020) active inclusion of patients has started in six centers; Radboud University Medical Center (Nijmegen, the Netherlands), Konstantopouleio General Hospital (Athens, Greece), Medisch Spectrum Twente (Enschede, The Netherlands) and Jeroen Bosch Hospital (Den Bosch, The Netherlands), University Medical Center Groningen (Groningen, The Netherlands), and University Hospital Ramón y Cajal (Madrid, Spain) and a total of 190 patients have been included. Four centers are preparing to start with inclusion; Inselspital Universitätsspital Bern (Bern, Switzerland), UCHealth University of Colorado Hospital (Denver, United States of America), Azienda Ospedaliera Universitaria Integrata Verona (Verona, Italy), and Policlinico A Gemelli (Rome, Italy). Inclusion of patients is expected to be finished December 2021.

## Discussion

The purpose of the DIA-PANC trial is to investigate the diagnostic accuracy of contrast-enhanced diffusion-weighted MRI in patients with suspected PDAC for the detection of liver metastases. Additionally, we will evaluate whether performing contrast-enhanced diffusion-weighted MRI will improve the detection of liver metastases compared to CECT by determining the sensitivity and specificity of CECT for the detection of liver metastases.

Despite the good diagnostic performance of MRI for liver metastases, the benefits of MRI remain unclear, mostly because of low level of evidence, heterogeneity, and bias in the performed studies. Two recently published meta-analyses have suggested the results should be confirmed by performing a well-designed and sufficiently powered study directly comparing liver CT and MRI in the same cohort [37, 38].

A major difficulty in the interpretation of the current literature is that most studies are retrospective often only reporting on a subset of patients actually undergoing a resection, patients with borderline resectable tumors, or patients with indeterminate liver lesions on CECT. These patients have a higher probability of having liver metastases. However, in an era of neoadjuvant therapy, local ablative therapy for advanced tumors, expensive targeted therapies, and resection of oligometastases, MRI may be beneficial to patients with all stages of PDAC. Therefore, all patients with suspected PDAC are eligible for inclusion in the DIA-PANC.

MRI field strength, 1.5 T versus 3 T, was a significant factor in the heterogeneity between studies that was found in a meta-analysis. 3 T MRI had a higher sensitivity (89%) and a lower specificity (88%) for diagnosing liver metastasis compared to 1.5 T MRI (sensitivity 80% and specificity 100%) [37]. Because the signal-to-noise ratio and the lesion-to-liver contrast are higher on 3 T MRI than on 1.5 T MRI, it is reasonable that a 3 T MRI permits a higher lesion detection rate [39, 40]. In the DIA-PANC study we plan to perform all MRIs on a 3 T scanner. A potential downside of a multicenter design is the intervendor variability that could occur when comparing the quantitative Apparent Diffusion Coefficient (ADC) value, this variability seems to be more pronounced at 3 T than at 1.5 T [41].

Availability of MRI is not expected to be an issue, as MRI is available in every expert center for pancreatic diseases. However, problems with MRI capacity could arise due to the need for MRI within a short interval after CT. A time interval of two weeks was chosen to provide a feasible time frame for MRI to be performed and no interval lesions are expected within this time interval [4].

The DIA-PANC trial is the first international prospective multicenter cohort study about the diagnostic accuracy of contrast-enhanced diffusion-weighted MRI. On the World Health Organization trial registry website (ICTRP), incorporating all (inter) national trial registries, there are only four other prospective trials registered in this field.

The first trial is a completed French prospective multicenter trial, presumably the only one prospective study that has been published [26]. The study has been performed in 118 patients with potentially resectable pancreatic cancer on a 1,5 T scanner using gadobenate dimeglumine (MultiHance) as contrast agent. The study has been performed to assess the diagnostic performance of diffusion-weighted MRI for the preoperative diagnosis of liver metastasis and the modification of therapeutic strategy as a consequence of the diagnosis of liver metastasis on diffusion-weighted MRI [42].

The second trial is a British single center observational study with a target sample size of 30 patients with confirmed or suspected pancreatic cancer referred for pancreaticoduodenectomy and is completed recently. The primary outcome of this study is the proportion of patients correctly identified by MRI to have lymph node, peritoneal, or liver metastases. To our knowledge, the results have not been published and there is no information on scan parameters and contrast agent available [43].

The third trial from Australia is the only randomized controlled trial. The study has a target sample size of 24 patients and is not yet recruiting. The aim of the study is to compare the 12-month recurrence rate in patients with locally operable pancreatic adenocarcinoma managed with standard preoperative assessment of liver metastases with CECT, versus preoperative assessment with liver specific contrast MRI [44].

The fourth trial is a Chinese comparative study and is not yet recruiting. The study aims to compare liver specific contrast MRI and CECT in liver metastasis of pancreatic cancer with a target sample size of 60 patients [45].

The DIA-PANC trial hypothesizes a superior value of MRI for the detection of liver metastases compared to CECT. To reliably determine the diagnostic accuracy the gold standard is histopathology of the liver lesions. Considering it is not always possible, and sometimes even unethical, to obtain histopathological proof of every lesion, follow-up is used as a reference standard. Hence, we are able to simultaneously gather information on (early) local recurrence or metastases after resection, disease progression, and therapy response evaluation on MRI and CECT.

In conclusion, the DIA-PANC trial is expected to report high-level evidence of the diagnostic accuracy of MRI for the detection of liver metastases compared to CECT, resulting in significant value for clinical decision making, guideline development and improved stratification for treatment strategies and future trials. Furthermore, DIA-PANC will contribute to our knowledge of liver metastases regarding incidence, imaging characteristics, their number and extent, and their change in time with or without treatment. When our hypothesis is confirmed, it will enhance the worldwide implementation of MRI and consequently improve personalized treatment of patients suspected of PDAC.

## Data Availability

The complete dataset will be property of the Sponsor, all participating institutions will own the dataset of the included patients from their center. Public access to the full trial protocol, trial-related documents, participant-level dataset, and statistical code may be made available on request.

## Abbreviations

ADC: Apparent Diffusion Coefficient
AJCC: American Joint Committee on Cancer
Castor EDC: Castor Electronic Data Capture
CEA: Carcinoembryonic Antigen
CECT: Contrast Enhanced Computed Tomography
CA19–9: Carbohydrate Antigen 19–9
DIA-PANC: Diagnostic accuracy of contrast-enhanced diffusion-weighted MRI for liver metastases of pancreatic cancer
DWI: Diffusion-Weighted Imaging
EORTC: European Organization for Research and Treatment
EUS: Endoscopic Ultrasound
FNA: Fine Needle Aspiration
FNB: Fine Needle Biopsy
Gd: Gadolinium
ICTRP: International Clinical Trials Registry Platform
MRCP: Magnetic Resonance Cholangio-Pancreatography
MRI: Magnetic Resonance Imaging
PDAC: Pancreatic ductal adenocarcinoma
SPSS: Statistical Package for the Social Sciences
TNM: Tumor, Node, Metastasis
WHO: World Health Organization
QLQ-C30: Quality of life questionnaire including 30 questions
QLQ-PAN26: Pancreatic cancer module of quality of life questionnaire including 26 questions
